### **3.7 Duration of patient follow up**

Each patient will be followed up actively after recruitment for 28 days (first follow up) and then passively for 6 months afterwards. If, within the 6-month period the patient will re-attend the health facility because of clinical malaria, he/she will be actively followed up for 28 days (second follow up) if inclusion and exclusion criteria are fulfilled, otherwise s/he will be treated with the first line drug or any other appropriate antimalarial. From the third episode of clinical malaria onwards, patients will be treated with the first line drug or any other appropriate antimalarial but will not be actively followed up.

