## *Methodology*

A multicentre, phase IV, randomized, open label, multi-arm study. Each patient will be actively followed for 28 days and then passively until 6 months after treatment. If, during the passive follow up, the patient experiences a second uncomplicated malaria episode, s/he will be treated with the same drug and actively followed up for additional 28 days.

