## 2. TRIAL OBJECTIVES AND PURPOSE

The main objective is to compare the safety and efficacy of 4 artemisinin-based combination therapies (ACT), i.e. amodiaquine-artesunate (AQ+AS), artemether-lumefantrine (AL), dihydroartemisinin-piperaquine (DHAPQ), chlorproguanil-dapsone-artesunate (CDA), for single and repeat treatments of uncomplicated malaria in African children. Safety will be determined by registering adverse events and grading, laboratory, and vital signs evaluations. Their incidence will be compared between the different study arms.

Specific objectives are the following:

1. To evaluate the efficacy of the 4 ACTs for the treatment of children with uncomplicated *P. falciparum* malaria (first active follow-up);
2. To determine after the first active follow-up the incidence rate of a second clinical episode of uncomplicated *P. falciparum* malaria;
3. To evaluate the efficacy of treating the second clinical episode of uncomplicated *P. falciparum* malaria with the same ACT used for the first one (second active follow-up);
4. To evaluate during the active and passive follow up the safety of the 4 ACTs for the treatment of children with uncomplicated *P. falciparum* malaria;
5. To establish the impact of using CDA on the selection of *P. falciparum* genotypes linked to SP resistance.

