All medication will be administered under observation by an authorised member of the study team (physician, clinician, or study nurse).

After the child has reached a study outcome, before or at the end (day 28) of the first active follow up, the parents or guardians will be encouraged to attend the health facility when the child is sick. If the child is not diagnosed with clinical malaria, s/he will be treated accordingly and parents or guardians will be asked to come back again whenever the child is sick. If the child has clinical malaria and meets the inclusion/exclusion criteria, s/he will be treated with the same drug received at the beginning of the first follow up and actively followed for 28 days according to the procedure outlined above. Re-treatment with the same study drug will be done at an interval of at least 29 days from the first treatment, i.e. after the first active follow up has finished. At the end of this second follow up, when one of the study

outcomes is reached, the child will be passively followed up until completion of the 6-month period started at the end of the first active follow up. Any malaria episode will be recorded and the patient treated with the standard antimalarial treatment. No active follow up will be carried out.

Patients will be assessed as summarized in the following flow-chart.

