#### ***3.10.2. Passive follow up (6 months after the first active follow up)***

Patients identified as treatment failures (clinical and parasitological) within the first follow up of 28 days will be treated with a full course of quinine or any other appropriate oral treatment (unrelated to the study drugs). Parents/guardians of children who have either been treated or classified as ACPR, i.e. with no malaria infection at day 28 of the first follow up will be asked to attend the health facility whenever the child is sick for the next 6 months. Each child will be visited monthly at home to keep the contact with the health facility. However, no data or blood slide will be collected unless the child is sick. Any attendance of children belonging to the cohort recruited for the first follow up will be recorded. The child will be clinically assessed and the medical history will be taken. Body temperature and a blood sample for

parasitaemia, Hb and PCR will be systematically collected. A diagnosis will be made and the child treated accordingly. Whenever an episode of uncomplicated malaria is diagnosed, the inclusion and exclusion criteria (section 3.8) will be checked and if these are fulfilled, the child will be re-treated with the same drug received for the first episode and will be followed up for the next 28 days (second active follow-up) with the same methodology as the first active follow-up. After the second active follow up, even if the child attend with an episode of clinical malaria fulfilling the inclusion/exclusion criteria, s/he will be treated with the local first line drug and no active follow up will be carried out after treatment. Children with a malaria infection but not fulfilling the inclusion and exclusion criteria will be treated with the local first line drug and their parents will be informed that they are still part of the cohort under passive surveillance. Children will reach the end of the study at the end of the 6-month passive follow up when they will be visited at home and the parents/guardians will be informed that the study is finished (Appendix VIII).

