### **5. PATIENT WITHDRAWAL CRITERIA**

Patients will be excluded from further assessment if there is withdrawal of informed consent. Severe adverse events related to the study drug are also a reason for withdrawal from the study drug but not withdrawal from study follow-up.

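### Entry to the second active follow-up is governed by rules that do not agree: episode count (3.7 against 3.10.2), end of the window (synopsis against body), and study-drug withdrawal (section 5)

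*Protocol*

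**What the plan says.** **Episode count.** Section 3.7 allows a second active follow-up for a clinical episode within the 6-month period if the criteria are met, and otherwise gives the first-line or another appropriate drug. It then adds: "From the third episode of clinical malaria onwards, patients will be treated with the first line drug or any other appropriate antimalarial", with no active follow-up.

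Section 3.10.2 has no count: "Whenever an episode of uncomplicated malaria is diagnosed, the inclusion and exclusion criteria (section 3.8) will be checked and if these are fulfilled", the child receives the same drug as before and is followed for 28 days. (The criteria are in section 3.9, not 3.8 as cited there.) A child whose infection does not meet the criteria gets the first-line drug, and "their parents will be informed that they are still part of the cohort under passive surveillance". Entry closes at a different point: "After the second active follow up, even if the child attend with an episode of clinical malaria fulfilling the inclusion/exclusion criteria", the local first-line drug is given without active follow-up.

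Section 4.1 adds that a child withdrawn from an active follow-up for a disallowed drug stays in passive follow-up and may start another active one. It states no limit.

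**Window.** Synopsis, Methodology: "Each patient will be actively followed for 28 days and then passively until 6 months after treatment". Section 3.8: "until completion of the 6-month period started at the end of the first active follow up". Section 3.7 and the heading of 3.10.2 agree with 3.8.

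**Withdrawal from study drug.** Section 5: "Severe adverse events related to the study drug are also a reason for withdrawal from the study drug but not withdrawal from study follow-up". Sections 3.8 and 3.10.2 direct re-treatment with the same drug whenever the criteria are met.

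**What these rules feed.** Objective 3 in section 2 begins: "To evaluate the efficacy of treating the second clinical episode of uncomplicated". Objective 2 is the incidence rate of a second clinical episode after the first active follow-up.

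**The concern.** These rules decide, at the clinic, who is re-treated with study drug and enters the second active follow-up. An analysis plan written later cannot undo that. If two sites follow different sections, the set of children behind objective 3 and the second-episode failure endpoint differs between sites for reasons unrelated to the drugs. Under section 3.10.2 that set can also include children treated for a third episode, although objective 3 speaks of the second.

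The end date sets both the last day on which a child can enter and the person-time for objective 2. The section 5 gap matters for the individual child: one section has stopped the drug, and two others direct its use again if a checklist is passed.

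**Working it through.** The protocol gives no figure for this point, so the check is a comparison of the texts plus one day count.

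**Step 1: episode count.** Apply each section to the same child.

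| Child | 3.7 | 3.10.2 | 4.1 |
|---|---|---|---|
| Second episode qualifies | Enters | Enters | – |
| Second episode does not qualify (e.g. parasitaemia below 2,000/µl), third does | Barred: third episode | Enters: no second active follow-up has taken place | – |
| Withdrawn from the second active follow-up for a disallowed drug, then a qualifying third episode | Barred: third episode | Unclear: an interrupted follow-up may or may not count as the second | Another active follow-up may start |

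Row 2 needs no interpretation. Section 3.7 counts episodes and section 3.10.2 counts active follow-ups. The counts part as soon as one episode passes without an active follow-up, and both sections provide for that case.

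**Step 2: window.** Inputs: first active follow-up of 28 days (3.7); re-treatment no earlier than 29 days after first treatment (3.8). Assumption: 6 months is m = 182 to 184 days, and the first active follow-up ends at day 28.

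- Synopsis: entry from day 29 to day m, length m − 28. With m = 183: 183 − 28 = 155 days (range 154 to 156).
- Sections 3.7, 3.8, 3.10.2: entry from day 29 to day m + 28, length m. With m = 183: up to day 211, 183 days (range 182 to 184).
- Difference: 28 days. 28/183 = 15.3% of the longer window (15.2% to 15.4% over the range).

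The same 28 days are the difference in maximum person-time per child for objective 2. The rate itself need not change by 15%, because events in those days enter or leave together with the time.

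**Step 3: section 5.** Take a child with a severe adverse event related to study drug who later has a new malaria episode with haemoglobin again at 7.0 g/dl or above.

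- Section 5: off study drug, still in follow-up.
- Section 3.9, which applies to both active follow-ups: no criterion names a previous related severe event. Two could apply: known hypersensitivity (exclusion 2), and a condition that the investigator judges to put the child at undue risk (exclusion 5).
- Sections 3.8 and 3.10.2: if neither is invoked, the same drug is given.

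The outcome therefore rests on discretion, and no rule refers back to section 5.

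**The case against.** **Section 3.7 may be shorthand.** Its third episode could mean any episode after the second active follow-up, which would agree with 3.10.2. That is possible, but 3.7 has just dealt with a re-attendance that does not qualify and then counts on to the third. A site reading it literally would bar the child.

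**The synopsis is a summary.** Three places in the body agree with one another, and the discrepancy applies equally to all arms. This stands: it is an editorial correction, not a source of bias between arms.

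**Section 5 is the specific rule and governs the general one, and exclusion 5 already lets the investigator keep the child out.** This stands in part. A reader might infer a flat contradiction that obliges re-treatment; the text does not support that, because exclusion 5 is available. But it is discretionary. Reading section 5 as limited to the current course would leave it with no effect on dosing for any event recognised after day 2, since dosing is on days 0 to 2.

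**A stronger reading on first-treatment failures.** A reader might infer that a late clinical failure in the first active follow-up is already the second episode, so that 3.7 bars the next one and the objective 3 population depends on first-treatment outcome, and so on arm. With 10% failure and an assumed half of failures clinical, that would give 5100 × 10% × 50% = 255 children. The documents do not support this. Objective 2, the endpoint of clinical malaria after the first active follow-up (3.3) and the synopsis all place the second episode after that period. Sections 3.8, 3.10.2 and 4.4 keep failures in the passive cohort. The figure falls with the reading, and would in any case be an upper bound, since not every such child returns with a qualifying episode.

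**Appendices VII and VIII are figures that could not be seen.** They may depict the pathway. They would not remove the disagreement in the text.

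**Conclusion.** The concern holds in three limited parts. The episode-count conflict between 3.7 and 3.10.2 is plain and gives opposite answers for a child with a non-qualifying second and a qualifying third episode; 4.1 adds a route with no stated limit. The end of the window differs by 28 days between synopsis and body, about 15% of the longer window, taking 6 months as 182 to 184 days. The relation between section 5 and same-drug re-treatment is a missing link left to discretion, not an outright contradiction.

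The number of children affected cannot be sized, because the protocol gives no expected rate of non-qualifying episodes, of repeat episodes or of related severe events. Selection differing by arm is not shown. The effect is confined to objectives 2 and 3, the second-episode endpoints and the safety of the few children to whom section 5 applies. The day-28 primary endpoints of the first follow-up and the sample size of 155 (170 with losses) per arm are untouched. It is worth correcting because it settles conduct at the site and costs little.

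**What to change.** Reconcile sections 3.7, 3.8, 3.10.2, 4.1 and 5 into one entry rule for the second active follow-up, and have the other sections refer to it. The sponsor decides the clinical content. The rule should state:

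- whether entry closes by number of episodes or by number of active follow-ups, and so what happens after a non-qualifying intervening episode;
- whether an active follow-up cut short under 4.1 counts;
- what applies to a child withdrawn from study drug under section 5;
- that a failure within the first active follow-up is not counted as a separate episode, as objective 2 implies.

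Use one end date for passive follow-up in the synopsis and the body, and correct the cross-reference in 3.10.2 to the criteria in 3.9.

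The cost is protocol wording and a line on the re-entry checklist. No visits, samples or patients are added.

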### **3.8 Follow-up Chart**

All children 6-59 months attending the outpatient clinic with fever or history of fever in the preceding 24 hours will have a thick and thin blood smear done. In sites where CDA is one of

the study drugs, the age range will be 12-59 months old. The parents or guardians of those with a *P. falciparum* infection of the required density will be informed by the health facility staff about the malaria clinical trial and will be requested to freely consent to participate in the trial. Unwillingness or inability to participate will result in the prescription and administration of the local standard treatment regime for uncomplicated *P. falciparum* malaria. The parents or guardians who accept their child to participate in the study will receive detailed explanations about the trial from the study staff. Specifically, they will be informed that three antimalarial drugs are being tested and the option given to the child will be decided randomly (by chance). They will be asked to sign (or thumb-print if illiterate) the informed consent form (see Appendix IV).

For children meeting the inclusion/exclusion criteria, the following steps will be taken:

1. A Case Report Form consisting of demographic and physical/clinical information will be completed;
2. Body weight and axillary temperature will be measured (the latter by using a digital electronic thermometer) and the results will be recorded on the Case Report Form. If the initial temperature value is less than 36°C the measurement will be repeated.
3. A thick blood smear will be obtained for measuring parasite density and a thin blood film for malaria species determination (the sample collected for screening can be used).
4. A blood sample will be collected on Whatman filter paper number 3MM for subsequent genotyping of the infective parasite strains. An additional blood sample to be later analysed for the determination of the G6PD status will be collected from all children in the sites where CDA is tested.
5. Blood sample (2 ml) for haematology/biochemistry will be taken.

At enrolment, children will be assigned a sequential study number. During the first 3 study days (days 0-2) patients will be admitted for observation and study drug administration. Parents/guardians will then be encouraged to return to the clinic for follow up assessments on days 3, 7, 14, 21, 28 and on any unscheduled day if the child is not well.

All medication will be administered under observation by an authorised member of the study team (physician, clinician, or study nurse).

After the child has reached a study outcome, before or at the end (day 28) of the first active follow up, the parents or guardians will be encouraged to attend the health facility when the child is sick. If the child is not diagnosed with clinical malaria, s/he will be treated accordingly and parents or guardians will be asked to come back again whenever the child is sick. If the child has clinical malaria and meets the inclusion/exclusion criteria, s/he will be treated with the same drug received at the beginning of the first follow up and actively followed for 28 days according to the procedure outlined above. Re-treatment with the same study drug will be done at an interval of at least 29 days from the first treatment, i.e. after the first active follow up has finished. At the end of this second follow up, when one of the study

outcomes is reached, the child will be passively followed up until completion of the 6-month period started at the end of the first active follow up. Any malaria episode will be recorded and the patient treated with the standard antimalarial treatment. No active follow up will be carried out.

Patients will be assessed as summarized in the following flow-chart.

**Figure 1. Follow up chart first and second active follow up.**

| Day                     | 0              | 1              | 2              | 3 | 4              | 5              | 6              | 7 | 14             | 21 | 28 | Any other day  |
|-------------------------|----------------|----------------|----------------|---|----------------|----------------|----------------|---|----------------|----|----|----------------------------|
| History                 | X              |                |                |   |                |                |                | X | X              | X  | X  | X                          |
| Informed consent        | X  |                |                |   |                |                |                |   |                |    |    |                            |
| Examination (clinical)  | X              | X              | X              | X |                |                |                | X | X              | X  | X  | X                          |
| Temperature             | X              | X              | X              | X |                |                |                | X | X              | X  | X  | X                          |
| Blood film              | X              | X              | X              | X |                |                |                | X | X              | X  | X  | X                          |
| Filter paper PCR        | X              | X              |                |   |                |                |                |   | X              | X  | X  | X                          |
| Filter paper G6PD**     | X              |                |                |   |                |                |                |   |                |    |    |                            |
| Adverse drug reactions  | X              | X              | X              | X | X  | X  | X  | X | X              | X  | X  | X                          |
| Concomitant medications | X              | X              | X              | X |                |                |                | X | X              | X  | X  | X                          |
| Haematology             | X              | X  | X  | X |                |                |                | X | X              |    | X  | X                          |
| Biochemistry*           | X              |                |                |   |                |                |                | X | X  |    | X  |                            |
| Treatment               | X              | X              | X              |   |                |                |                |   |                |    |    |                            |

 Spontaneous attendance to health facility;  Only at the beginning of the first follow up.  In sites where CDA is tested, Hb will be determined also at day 1 and 2 after treatment and for the three arms of the study;  If abnormal at day 7.  If the patient attends spontaneously the health facility.

\*Not all sites; \*\*Only in sites where CDA is tested.

### 3.9 Selection of the Patients (for the first and second active follow up)

#### Inclusion criteria

In order to be eligible, patients should satisfy the following inclusion criteria:

1. Males and Females aged between 6 months and 59 months inclusive. In the sites where CDA is tested all recruited children will be aged between 12 months and 59 months inclusive. This criterion applies only for the recruitment in the first follow up. For the second follow up, children having been included in the first follow up are eligible, regardless of their age.
2. Body weight of 5 Kg and above.
3. Microscopically confirmed, monoinfection of *Plasmodium falciparum* (parasitaemia  $\geq 2,000/\mu\text{L}$  to  $200,000/\mu\text{L}$ ).
4. Fever (axillary temperature at  $\geq 37.5^\circ\text{C}$ ) or history of fever in the previous 24 hours.
5. Haemoglobin value  $\geq 7.0$  g/dl;
6. Signed (or thumb-printed whenever parents/guardians are illiterate) informed consent

by the parents or guardians. Note the informed consent will be asked only at recruitment and will cover the whole period of the study, including second active follow up and passive case detection.

7. Parents' or guardians' willingness and ability to comply with the study protocol for the duration of the trial.

### **Exclusion criteria**

Patients with any of the following criteria will not be admitted to the study:

1. Participation in any other investigational drug study (antimalarial or others) during the previous 30 days.
2. Known hypersensitivity to the study drugs.
3. Severe malaria.
4. Danger signs: not able to drink or breast-feed, vomiting (> twice in 24hours), recent history of convulsions (>1 in 24h), unconscious state, unable to sit or stand.
5. Presence of intercurrent illness or any condition (cardiac, renal, hepatic diseases) which in the judgement of the investigator would place the subject at undue risk or interfere with the results of the study, including known G6PD deficiency.
6. Severe malnutrition (defined as weight for height <70% of the median NCHS/WHO reference).
7. Ongoing prophylaxis with drugs having antimalarial activity such as cotrimoxazole for the prevention of *Pneumocisti carini* pneumonia in children born to HIV+ women.

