### **Diagnosis and Main Inclusion Criteria**

Children 6-59 months old (this criterion applies only for the first active follow up) (in sites testing CDA the age group for the 3 study arms will be 12-59 months) with suspected uncomplicated clinical malaria attending the health facility where the study is carried out will be recruited into the study and randomised to one of the study treatments if they fulfil all the following inclusion criteria: 1. Weight > 5 kg; 2. Mono-infection with *P. falciparum* and a parasitaemia of 2,000–200,000 asexual parasites per µl; 3. Fever (axillary temperature ≥37.5 °C) or history of fever in the preceding 24 hours; 4. Haemoglobin value ≥ 7.0 g/dl; 5. Signed informed consent by the parents or guardians; 6. Parents' or guardians' willingness and ability to comply with the study protocol for the duration of the trial.

They will be excluded if they have at least one of the following criteria:

- Participation in any other investigational drug study (antimalarial or others) during the previous 30 days
- Known hypersensitivity to the study drugs
- Severe malaria\*.
- Danger signs: not able to drink or breast-feed, vomiting (> twice in 24hours), recent history of convulsions (>1 in 24h), unconscious state, unable to sit or stand;
- Presence of intercurrent illness or any condition (cardiac, renal, hepatic diseases) which would place the subject at undue risk or interfere with the results of the study, including known G6PD deficiency.
- Severe malnutrition (defined as weight for height <70% of the median NCHS/WHO reference)
- Ongoing prophylaxis with drugs having antimalarial activity such as cotrimoxazole for the prevention of *Pneumocystis carinii* pneumonia in children born to HIV+ women.

\*WHO 2000: Severe falciparum malaria. *Trans. R. Soc. Trop. Med. Hyg.* **94**, 1-90.

Children infected with other malaria species and those with mixed malaria infections will be excluded from the study but adequate treatment will be provided. Cases of severe and complicated malaria will be referred to hospital for treatment with intravenous quinine and other supportive therapy.

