#### \* Early Treatment Failure (ETF) (one of the following)

- (i) Development of danger signs or severe malaria (see Appendix V) on Day 0, Day 1, Day 2 or Day 3, in the presence of parasitaemia,
- (ii) Parasite density on Day 2 > Day 0 count, irrespective of axillary temperature,

- (iii) Presence of parasitaemia on Day 3 with fever (axillary temperature  $\geq 37.5^{\circ}\text{C}$ ),
- (iv) Parasitaemia on Day 3  $\geq 25\%$  of count on Day 0.

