#### Late Clinical Failure (LCF):

- (i) Development of danger signs or severe malaria after Day 3 in the presence of parasitaemia, (See Appendix V for the criteria of severe malaria/danger signs).
- (ii) Presence of parasitaemia and fever on any day from Day 4 to Day 28, without having previously meet the criteria of ETF.

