#### **4.4 Rescue Treatments**

Active follow up of patients with treatment failure, including parasitological failure, will be stopped and they will be treated with rescue treatment. This consists in quinine 10 mg/kg orally three times a day for 7 days or an antimalarial treatment according to the country's national guidelines. Any patient, who is diagnosed with severe malaria or danger signs during follow-up, will be referred for treatment with parenteral quinine and supportive measures at the local facility or hospital. After the rescue treatment the patient will still be considered in the passive follow up until completion of the 6-month period.

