## APPENDIX V

### Criteria for Severe Malaria/Danger Signs

#### **Severe Malaria**

- Unarousable coma (*if after convulsion, > 30 min*)
- Repeated convulsions (*> 2 within 24 h*)
- Severe anaemia (*Hb < 5.0 g/dL*)
- Respiratory distress (*laboured breathing at rest*)

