#### **Danger Signs**

- Recent convulsions (*>1 within 24 h*)
- Altered consciousness (*confusion*)
- Lethargy
- Unable to drink or breast feed
- Vomiting everything
- Unable to stand/sit due to weakness

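### Exclusion 4 omits two of the protocol's own Appendix V danger signs, lethargy and altered consciousness, so no explicit, non-discretionary criterion in the text shown keeps such a child off oral study drug

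*Protocol*

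**What the plan says.** Exclusion 4 in section 3.9 reads "Danger signs: not able to drink or breast-feed, vomiting (> twice in 24hours), recent history of convulsions (>1 in 24h), unconscious state", and ends with inability to sit or stand. The synopsis carries the same list. Neither place points to Appendix V. Section 3.9 governs both the first and the second active follow-up.

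Appendix V has a separate danger-sign list of six items. One is "Altered consciousness (*confusion" and another is lethargy. Its severe-malaria list has a single consciousness item, "Unarousable coma (*if after convulsion, > 30 min".

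Section 3.2 uses Appendix V for the outcome. Early failure includes "Development of danger signs or severe malaria (see Appendix V) on Day 0, Day 1, Day 2 or Day 3", with parasitaemia. For late clinical failure the text says "See Appendix V for the criteria of severe malaria/danger signs".

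Section 4.4 sets the clinical response: "Any patient, who is diagnosed with severe malaria or danger signs during follow-up, will be referred for treatment with parenteral quinine".

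At screening, the synopsis says "Cases of severe and complicated malaria will be referred to hospital for treatment with intravenous quinine". For a later episode, section 3.8 says "If the child has clinical malaria and meets the inclusion/exclusion criteria, s/he will be treated with the same drug received at the beginning", meaning the drug given for the initial episode.

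**The concern.** The protocol has two danger-sign lists that do not agree. The shorter one decides who may receive oral study drug. The longer one decides who has failed treatment.

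Take a child who is lethargic or confused but can drink, sit and stand. Exclusion 4 does not bar this child. If the same sign is diagnosed in follow-up, section 4.4 calls for referral for parenteral quinine, and with parasitaemia it counts toward treatment failure. Sites must settle the difference by judgement, and must do so again at re-treatment because the same criteria apply.

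What is at stake is the safety of young children at entry (6-59 months, or 12-59 months where CDA is tested) and consistent practice across 10 sites in 7 countries. Eligibility is fixed in the protocol, so an analysis plan would not be expected to repair it.

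**Working it through.** No figure in the plan depends on this point, so the check is a comparison of texts.

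**Step 1. Compare the two lists.**

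| Appendix V danger sign | Exclusion 4 | Result |
|---|---|---|
| More than one convulsion in 24 h | Same threshold | Match |
| Cannot drink or breast-feed | Same | Match |
| Cannot stand or sit | Same | Match |
| Vomits everything | More than twice in 24 h | Replaced |
| Altered consciousness (confusion) | None | Absent |
| Lethargy | None | Absent |

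That is 3 matches + 1 replacement + 2 absent = 6. Exclusion 4 also has an unconscious state, which is graver than either missing sign and does not cover it. The vomiting count suits oral dosing and is not a defect.

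**Step 2. Look for another criterion that closes the gap.**

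- *Exclusion 3, severe malaria.* In Appendix V only unarousable coma concerns consciousness, so lethargy or confusion does not qualify. The synopsis footnotes this exclusion to a WHO 2000 document instead. Its content is not reproduced, so whether it covers these signs cannot be checked here.
- *Exclusion 5.* It depends on the investigator's judgement and does not name these signs.
- *Restriction to uncomplicated malaria.* It applies at entry (synopsis, inclusion criteria). At re-treatment it appears in the synopsis methodology, specific objective 3 and section 3.10.2. Sections 3.7 and 3.8 speak of clinical malaria plus the criteria, which does not lift the limit. The text does not define uncomplicated or complicated in terms of these signs.
- *Admission on days 0-2 and observed dosing* (sections 3.8 and 3.12). These reduce risk after enrolment but do not decide who is enrolled.
- *Appendices VI and VII*, the enrolment and critical-steps charts. They are not shown in the copy reviewed and could not be checked.

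Some of these filters would keep a lethargic or confused child out. None that can be read names either sign as a mandatory exclusion.

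**Step 3. Check whether the signs can already be seen at entry.** The Day 0 examination (section 3.10.1) refers to Appendix I. Table A there grades confusion under behavioural changes, and Table C lists lethargy under severe dehydration. No new examination would be needed.

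**Step 4. Cost of closing the gap.** The documents do not give the share *s* of otherwise eligible children with either sign, so *s* is an assumption. Section 3.1 gives 510 enrolled per site. Children needed = 510/(1 - *s*), rounded up:

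- *s* = 1%: 510/0.99 = 515.2, so 516 (6 more)
- *s* = 2%: 510/0.98 = 520.4, so 521 (11 more)
- *s* = 5%: 510/0.95 = 536.8, so 537 (27 more)

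**The case against.** The strongest reply is that the child in question is rare and already well guarded. The child must be lethargic or confused, yet conscious, drinking, able to sit and stand, not vomiting more than twice, without repeated convulsions, with haemoglobin of at least 7 g/dl, diagnosed as uncomplicated, and not judged at undue risk. Such a child is then admitted and dosed under observation, and a danger sign diagnosed in follow-up prompts referral. Appendix V sets no threshold for lethargy, and Appendix I grades even mild confusion or agitation, so a hard exclusion moves some of the judgement elsewhere.

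Much of this stands. It limits the size of the problem and rules out several stronger readings that a reader might infer:

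- *That nothing in the protocol keeps such a child off study drug.* The documents do not support this. The uncomplicated-malaria limit, exclusion 3 with its unreproduced WHO source, and exclusion 5 may all do so, and two charts could not be checked.
- *That a child enrolled with the sign is automatically an early failure on Day 0.* The definition speaks of signs developing, so a sign already present at entry is not clearly covered.
- *That sections 3.8 and 4.4 give contrary orders for a returning child.* This holds only if follow-up in section 4.4 includes the passive phase at the moment of a new episode, which the text does not settle.

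The objection does not explain why the entry list should differ from the list the protocol itself cites for danger signs.

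**Conclusion.** The inconsistency is real and should be corrected. Two of six Appendix V danger signs are missing from exclusion 4, and no explicit, non-discretionary criterion in the text shown excludes a child with either one, at first treatment or at re-treatment.

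The comparison rests only on the wording of exclusion 4, Appendix V and sections 3.2 and 4.4. The conclusion about other safeguards is limited to the text available. The number of children affected cannot be estimated from the documents and is probably small. A reader might infer distorted efficacy results or a bias between arms; nothing in the documents shows either, since all arms at a site share the same entry rule.

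**What to change.** Reword exclusion 4 in section 3.9 and in the synopsis to: *any danger sign in Appendix V, unconscious state, or vomiting more than twice in 24 hours*. This adds the two missing signs and keeps the vomiting count and the unconscious-state item.

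The cost is one line in two places and some additional screening exclusions: 6 to 27 per site under the assumed shares of 1% to 5%, with the true share unknown. Because Appendix V does not define lethargy, sites should apply the same working reading at entry as they use for treatment failure. The cross-reference makes the two uses consistent but does not supply that definition.
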